### Randomization and allocation

2.6

The random number list will be generated through Statistical Product and Service Solutions 22.0 (IBM SPSS) in a 1:1 ratio by a trained statistician. A stratified random method will be used to balance the patients within hospitals and the stratification factor will be the 4 study centers. The list contains 2 corresponding columns, 1 is the sequence number of inclusion, the other 1 is the treatment or placebo group. This statistician will contact the pharmaceutical factory and give them this randomization list. The factory than will stick the sequence number label on boxes of NBZG or placebo as the list. The statistician and pharmaceutical factory will store the randomization list to maintain concealment. And the other investigators will not know the corresponding relations between sequence numbers and different groups until the trials completed.

Medicine (NBZG or the placebo) with labels will be stored in a locked and appropriate room. A trained administrator will charge the medicine and the key. And this administrator also will charge the assignment of participants to interventions.

When a participant is recruited in, the investigator will make a central telephone call and give him/her the medicine (NBZG or the placebo) from the administrator according to the central call.

### Blinding

2.7

The stuff in the pharmaceutical factory only provides drugs and random number list, and never participates in the trial. The investigators, clinicians, nurses, outcome evaluators, statisticians, and participants have no idea about the group assignment information until the entire trial is completed.

When an adverse event is claimed, we will record it and provide an appropriate treatment. Clinicians will provide emergency services in case of serious adverse events, and report them to the Institutional Review Board within 24 hours. Then the blinding will be broken by the main trial investigator, leader of Longhua Hospital ethic committee and the statistician to provide participant information of intervention, NBZG or NBZG placebo.

### Outcomes

2.8

#### Primary outcomes

2.8.1

The ACR50 rate after 12 weeks’ treatment was compared to that at baseline in the 2 groups. The ACR50 is a scale to measure change in RA symptoms,^[10]^ which have been used for testing the effectiveness of clinical interventions in large-sample groups,^[11,12]^ ACR 50 is met when the number of tender joints reduces by ≥50%, the number of swollen joints by ≥50%, and at least 3 of the following 5 indexes improved by ≥50%:

Patient's arthritis pain using a visual analog scale (VAS) of 0 to 100 mmPatient's disease activity using VAS (0–10)Patient's physical function and disability using Health Assessment Questionnaire - Disability Index (HAQ-DI)Acute-phase reactant value such as erythrocyte sedimentation rate (ESR) or C-reactive protein level

Similarly, ACR20 is met when ≥20% is achieved in the reduction of tender joint number, swollen joint number, and the rise of the score of at least 3 of another 5 indexes.

Although compared to ACR50 and ACR70, ACR20 has been accepted as a benchmark in RA clinical trials for its capacity to distinguish active treatment from placebo control,^[13,14]^ ACR50 is still a preferred cutoff than ACR70 to evaluate RA.^[11]^ Here, we choose ACR50 to measure the primary outcome.^[11,15]^

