**Methods::**

A multicenter, randomized, double-blind, placebo-controlled clinical trials will be conducted to determine the efficiency of NBZG in pain relief and joint protection. A total of 120 patients with active RA will be enrolled, and treated with NBZG or placebo for 12 weeks. The primary outcome measurements include rate of American College of Rheumatology (ACR) 50 at 12 weeks’ treatment. The 2nd outcome measurements include rate change of ACR20, ACR70, the disease activity score (DAS) 28, 36-item Short-Form Health Survey Questionnaire, Health Assessment Questionnaire - Disability Index, score changes of Patient Assessment of Arthritis Pain, Patient Global Assessment of Arthritis, and the Athens insomnia scale at the same time points.

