### Sample size calculation

2.4

We calculated the sample size according to our primary study. We conducted a preliminary experiment from November 2016 to July 2017 into the efficacy of the NBZP combined with MTX vs MTX alone, and we found that patients taking the NBZP combined with MTX achieved 84.8% American College of Rheumatology (ACR) 50, whereas patients in the MTX group achieved 55.5% ACR50 response. The formula to calculate the rate in completely random design is: 

n1 and n2 are the patient numbers in NBZG group and placebo group; 
[figure not shown]
 when type 1 error is 0.05, *u*_*β*_ = 1.282 when type II error is 0.1 in 2-sided tests. 

 is the mean of *p*_1_ and *p*_2_.^[7]^ Approximately 120 participants are needed to achieve a 90% power and a (2-sided) 5% significance level in detecting the therapeutic differences between 2 groups. Thus, the final sample size has been set as 120 patients (60 per group), considering 20% dropout rate.

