### Statistical analysis

2.14

All data analyses will be performed using Statistical Packages of Social Sciences (SPSS) software (version 22.0). Continuous data are presented as mean ± standard deviation (SD) and categorical data as frequencies. Continuous variables following the normal distribution will be analyzed by Student *t* test; otherwise, nonparametric tests will be used to compare group differences. Statistical test is 2-sided and *P*-value <.05 will be defined as statistically significant. We will adopt intention-to-treat approach and last-observation-carried-forward method will be applied in the missing values.

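### The primary outcome section compares the week-12 ACR50 rate with baseline, where that rate is zero by definition. This contradicts the between-group sample size, and no named test is tied to the binary primary endpoint.

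*Protocol article*

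**What the plan says.** - **Primary outcomes (2.8.1):** the ACR50 rate after 12 weeks of "treatment was compared to that at baseline in the 2 groups". The same section defines the response as improvement: "ACR 50 is met when the number of tender joints reduces by ≥50" percent, with a matching fall in swollen joints and improvement in at least 3 further indexes.
- **Abstract, Methods:** the primary measure is the "rate of American College of Rheumatology (ACR) 50 at 12 weeks", with no comparison to baseline.
- **Sample size calculation (2.4):** a two-rate formula with pilot ACR50 rates of 84.8% and 55.5%, set for "a 90% power and a (2-sided) 5% significance level" in "detecting the therapeutic differences between 2 groups". The result is 60 per group after a 20% dropout allowance.
- **Statistical analysis (2.14):** continuous variables get the Student t test if normal; "otherwise, nonparametric tests will be used to compare group differences". For binary data the section says only that it presents "categorical data as frequencies".
- **Randomization and allocation (2.6):** "the stratification factor will be the 4 study centers". Section 2.14 does not mention centre.

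**The concern.** A responder rate defined by change from baseline has no baseline value other than zero. Setting the week-12 rate against it asks only whether anyone responded. Both arms receive methotrexate, so the answer would almost certainly be yes in both, whatever the granule does. Read literally, the section that defines the primary outcome specifies a comparison that is not a treatment comparison, and it leaves room for a within-group efficacy claim.

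The analysis section does not resolve this. It does assign tests, but to continuous variables, while the primary endpoint is yes/no. The trial's one confirmatory claim therefore rests on a comparison that contradicts the sample size section and on a test that the reader has to guess.

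**Working it through.** **1. Which comparison was powered.** Inputs from section 2.4: p1 = 0.848, p2 = 0.555, two-sided 5% (z = 1.96), 90% power (z = 1.282). The difference is d = 0.293 and the mean rate is 0.7015.

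n per arm = [1.96·√(2·0.7015·0.2985) + 1.282·√(0.848·0.152 + 0.555·0.445)]² / 0.293²
= (1.268 + 0.786)² / 0.0858 = 49.2, so 50.

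Then 50 × 1.2 = 60 per arm, 120 in total. The protocol's figure is reproduced as a between-arm comparison of two proportions. (Dividing by 0.8 would give 63 per arm; that is a separate matter.)

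**2. What 2.8.1 does if followed literally.** With a baseline rate of 0, all discordant pairs in an arm go one way, so the exact two-sided McNemar p-value with b responders is 2 × 0.5^b.
- b = 5: p = 0.0625. b = 6: p = 0.031. Six responders are enough.
- Probability of at least 6 responders among 60 in the placebo plus methotrexate arm: above 0.9999 at the protocol's 55.5%, and 98.8% at an assumed 20%.

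**3. What the between-arm test does.** Power = Φ{[0.293·√n − 1.268] / 0.613}.
- n = 60 per arm: Φ(1.63) = 94.9%.
- n = 48 per arm (20% lost): Φ(1.24) = 89.3%.

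Stating the between-arm comparison leaves N = 120 as it is.

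**4. Does leaving out centre invalidate the test?** Simulation of 40,000 trials per scenario, with 15 patients per arm in each of 4 centres. The equal centre sizes, the log-odds step between neighbouring centres and the 75% rate are assumptions.

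| Log-odds step | Type I error: chi-square / CMH | Power, 84.8% vs 55.5%: chi-square / CMH | Power, 75% vs 55.5%: chi-square / CMH |
|---|---|---|---|
| 0 | 5.4% / 5.4% | 95.4% / 95.1% | 62% / 62% |
| 0.5 | 4.5% / 4.9% | 95.8% / 96.1% | 62% / 65% |
| 1.0 | 2.8% / 5.0% | 97.0% / 98.0% | 63% / 72% |

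Ignoring centre makes the test conservative when centres differ; it does not raise the error rate above that of CMH. A t test or rank-sum test on the 0/1 data had the same simulated type I error as the chi-square.

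**5. Baseline adjustment of continuous secondary outcomes.** With equal variances at both times and correlation ρ, the ANCOVA variance is (1 − ρ²) of that for week-12 values, and (1 − ρ²)/[2(1 − ρ)] = (1 + ρ)/2 of that for change scores. The protocol gives no ρ, so the values below are assumptions.

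| ρ | Reduction vs week-12 values (ρ²) | Reduction vs change scores (1 − (1 + ρ)/2) |
|---|---|---|
| 0.3 | 9% | 35% |
| 0.5 | 25% | 25% |
| 0.7 | 49% | 15% |

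**The case against.** The best defence is that the 2.8.1 sentence is loose drafting. It may mean only that each patient's week-12 state is judged against that patient's own baseline, which is what ACR50 does. The abstract states the endpoint without a baseline comparison, section 2.4 is plainly between-group, and 2.14 speaks of group differences. The nonparametric clause might also have been meant to cover proportions, and further detail may sit in an analysis plan that is not shown.

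Much of this stands. The between-group question is stated elsewhere, and it is probably what is intended. But the section that defines the primary outcome still says something different, and that contradiction lies within the document, whatever an analysis plan adds. The nonparametric clause follows from a sentence about continuous variables. Even on the generous reading it names no particular test for ACR50.

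A reader might also infer that the primary question has no valid test because the centre strata and baseline values are ignored. The documents do not support that:
- Leaving out centre does not inflate type I error. At the design rates it changes power by about 1 point at most.
- Baseline is already built into ACR50.
- For the continuous outcomes, sections 2.9.1 to 2.9.5 describe assessment from baseline to later visits, and the abstract lists score changes for pain and global assessment. Baseline may therefore enter through change scores, and a t test on change is valid in a randomised trial.

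**Conclusion.** The point holds for the primary comparison. Section 2.8.1 words it as week 12 against baseline, which is degenerate for a responder endpoint and contradicts the comparison on which section 2.4 sized the trial. Section 2.14 assigns tests only to continuous variables. The within-arm threshold of 6 responders follows from the ACR50 definition alone. The probability above 0.9999 uses the protocol's 55.5%, and the 98.8% uses an assumed 20%. Because this governs the trial's single confirmatory claim, it should be corrected before unblinding.

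Centre stratification and baseline adjustment are improvements in efficiency only. Their size depends on assumed centre spread and assumed correlations, and the ANCOVA gain applies to the continuous secondary outcomes, not to the endpoint on which 120 was calculated.

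**What to change.** 1. **Section 2.8.1:** replace the sentence with a statement that the proportion of patients with ACR50 at week 12 will be compared between the NBZG and placebo groups.
2. **Section 2.14:** name a between-arm test of proportions for ACR50, preferably Cochran-Mantel-Haenszel stratified by the 4 randomisation centres, with a risk difference and 95% CI. Use the same for ACR20 and ACR70.
3. **Separately, for efficiency:** analyse DAS28, HAQ-DI, the pain and global scales, AIS and SF-36 by ANCOVA with baseline value and centre, in place of a t or rank test chosen by a look at normality.

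Items 1 and 2 need a few sentences. Item 3 changes the named analysis of every continuous secondary outcome, so it is a larger edit. None of them needs new data, because baseline values and centre are already recorded. N remains 120.

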### Secondary outcomes

2.9

The secondary outcome parameters include the DAS28, rate of ACR20/70, HAQ-DI, 36-item Short-Form Health Survey Questionnaire (SF-36), Patient Assessment of Arthritis Pain, Patient Global Assessment of Arthritis, and Athens insomnia sleep scale.

#### DAS28: from baseline to weeks 4, 8, 12, and 16

2.9.1

The DAS28, a widely used indicator to evaluate RA disease activity after treatment, was published in 1993 by van der Heijde et al.^[16]^ DAS includes the following 4 measurements^[17]^: the counts of swollen and painful joints, the ESR, and a measurement for general health (GH). The formula of DAS28 is 

 The 28 joints include 10 proximal interphalangeal joints and 10 proximal interphalangeal joints of hands and wrists, elbows, knees, and shoulders bilaterally. GH is patient GH VAS (0–10 mm). Using this formula, DAS28 <2.6 signifies remission.

#### HAQ-DI (from baseline to weeks 4, 8, 12, and 16)

2.9.2

The HAQ-DI, a modification of ACR20/50/70, is efficient to assess functional status of the patient attacked by chronic illness,^[12]^ like RA.^[18]^

There are 20 questions that describe 8 movements: dress, rise, eat, walk, hygiene, reach, grip, and usual activities. Each question is followed by 4 choices: without any difficulty (0 point); with some difficulty (1 point); with much difficulty (2 points); and unable to do (3 points). HAQ-DI score is the average of 8 sections’ scores ranging between 0 and 3, higher score representing more severe disability. Generally, HAQ-DI score of 0 to 1 indicates mild to moderate difficulty; 1 to 2 indicates moderate to severe disability; 2 to 3 indicates severe to extremely severe disability.^[19]^

#### Patient assessment of arthritis pain and patient global assessment of arthritis (from baseline to weeks 4, 8, 12, and 16)

2.9.3

Patient assessment of arthritis pain and patient global assessment of arthritis are 2 subscales of ACR 20/50/70 and use a VAS of 0 to 100 mm.^[12]^

#### Athens insomnia scale (from baseline to weeks 4, 8, 12, and 16)

2.9.4

Most patients with RA report poor sleep,^[20]^ which may be induced by pain, fatigue, depression,^[21]^ and inflammation.^[22]^ Athens insomnia scale (AIS), a useful tool in sleep research and clinical practice, consists of 8 items: sleep induction, awakenings during the night, final awakening, total sleep duration, sleep quality during the night, emotion during the day time, functioning capacity, and sleepiness during the day time.^[23]^ Each item gives 0 to 3 points, with 0 representing no problem at all and 3 representing very serious condition. Thus, the total maximum score is 24 which means the most severe degree of insomnia. The lower score indicates the better sleep quality.^[24]^

#### SF-36 (from baseline to weeks 4, 8, 12, and 16)

2.9.5

The SF-36 is a tool for assessing physical status of patients with RA.^[25–27]^

SF-36 consists of 36 items in 8 types, including physical function, role physical, bodily pain, and global health, vitality, social function, role emotional, and mental health.^[28]^

### Safety assessments

2.10

To assure the safety of participants, the data collection process will be supervised by the project director. The patients’ blood routine, urine routine, feces routine, kidney, and liver function will be tested on schedule. At each visit, patients will be asked about the adverse effects during the study period. To protect their privacy, all participants will be visited in a closed room. Participants can raise questions and withdraw at any time.

### Participant timeline

2.11

Recruitment will start in February 2019 and end in February 2020. The last visit will be finished before March 31, 2021. The recruitment process is shown in Figure 1, and the schedule is shown in Table 1 table 1.

**Figure 1 F1:**
[figure not shown]
Project overview. RA = rheumatoid arthritis, NBZG = Jia Wei Niu Bang Zi granule.

**Table 1 T1:**
[figure not shown]
Schedule of enrollment and assessments.

### Data collection and monitoring

2.12

During this 16-week trial, all participants will be treated with NBZG or NBZG placebo for 12 weeks follow-up for 4 weeks. Five rounds of disease activity assessments (the baseline, week 4, week 8, week 12, and week 16) and 5 rounds of safety assessments (the baseline, week 4, week 8, week 12, and week 16) will be recorded in Epidata (Version 3.1) by 2 statisticians independently. Disagreement will be solved by discussion and a third statistician.

Longhua Hospital Affiliated to Shanghai University of Traditional Chinese Medicine (http://www.longhua.net/ywsy/gzlc/287.jhtml) control the quality.

### Quality control

2.13

Training will be carried out before the trial to let the involved physicians, nurses, and evaluators from the multicenter fully apprehend the process of the entire trial. When the trial starts, several investigators will be sent to 4 centers every month to assure whether: each center recruits enough participants in the plan; all participants meet the inclusion criteria and do not meet the exclusion criteria; all the participants fully follow the clinical trial process, and the case report form (CRF) has been completed. At the same time, we will call every participant to check the CRF and put its information into the e-database of CRF monthly. Epidata (version 3.0) procedure will be used to restrict data values. Two investigators will enter and compare the data independently to rule out the difference.

### Statistical analysis

2.14

All data analyses will be performed using Statistical Packages of Social Sciences (SPSS) software (version 22.0). Continuous data are presented as mean ± standard deviation (SD) and categorical data as frequencies. Continuous variables following the normal distribution will be analyzed by Student *t* test; otherwise, nonparametric tests will be used to compare group differences. Statistical test is 2-sided and *P*-value <.05 will be defined as statistically significant. We will adopt intention-to-treat approach and last-observation-carried-forward method will be applied in the missing values.

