We will call the patients to take laboratory tests to record in a notebook the medicine they have used. When serious adverse effects occur, we will provide an appropriate treatment to the patient immediately, record the adverse effect, and stop medicine.

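### LOCF for every missing value lets an early responder who is then lost count as a week-12 ACR50 responder, and can bias the primary comparison in either direction

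*Protocol article*

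**What the plan says.** The only missing-data rule is in section 2.14 (Statistical analysis): "We will adopt intention-to-treat approach and last-observation-carried-forward method will be applied in the missing values". It applies to all outcomes alike, and the same section analyses normally distributed continuous variables by t test.

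The primary endpoint is binary. Section 2.8.1 defines ACR50 after 12 weeks of treatment and states: "Here, we choose ACR50 to measure the primary outcome".

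Section 2.12 provides the earlier values that could be carried: "Five rounds of disease activity assessments (the baseline, week 4, week 8, week 12, and week 16". Sections 2.9.1 to 2.9.3 schedule the ACR components at weeks 4 and 8: joint counts and ESR through DAS28, HAQ-DI, pain and patient global assessment.

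The plan expects sizeable loss. Section 2.4: "Thus, the final sample size has been set as 120 patients (60 per group), considering 20% dropout rate". Section 2.10 allows withdrawal at any time. For serious adverse effects, the text on interventions says staff will "record the adverse effect, and stop medicine"; it does not say that follow-up ends.

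**The concern.** LOCF answers a different question from the one the primary endpoint asks. The endpoint is response at week 12. For a patient lost after week 4 or 8, LOCF substitutes response at the last visit attended and assumes that nothing changed afterwards. For a binary responder endpoint, this credits a success that nobody observed.

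If the two arms lose the same share of patients, and those patients had the same last-visit response, the credit cancels in the difference and only the two absolute rates are raised. If the arms differ in either respect, the difference moves. Such differences are plausible in a placebo-controlled add-on trial, where the reasons for leaving (intolerance, lack of effect) may not be the same in both arms.

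For the continuous scores, LOCF freezes disease activity at the last visit. The t test then treats carried values as measured week-12 values, so imputation uncertainty is left out of the standard error.

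**Working it through.** **Inputs from the article.** Pilot ACR50 rates (section 2.4): "patients taking the NBZP combined with MTX achieved 84.8% American College of Rheumatology (ACR) 50" and "patients in the MTX group achieved 55.5% ACR50 response", so p1 = 0.848, p2 = 0.555 and the planned difference is 29.3 points. Two-sided 5% level, 90% power, 60 per arm, 20% dropout (section 2.4).

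**Assumed, not in the article.** Dropout by arm (d1 for NBZG, d2 for placebo) and the share of dropouts whose last attended visit met ACR50 (q1, q2).

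**1. The plan's own figure.** With pooled variance under the null and no continuity correction,

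n = [1.96·√(2·p̄(1−p̄)) + 1.282·√(p1(1−p1) + p2(1−p2))]² / (p1−p2)²

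with p̄ = 0.7015: n = [1.96·√0.4188 + 1.282·√0.3759]² / 0.293² = 2.054² / 0.0858 ≈ 49.2, so 50 per arm. Then 50 × 1.2 = 60 per arm, 120 in total. The stated size reproduces.

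**2. Patients affected.** 0.20 × 60 = 12 per arm. Relative to counting dropouts as non-responders, LOCF adds d × q to an arm's rate. At 20% dropout this lies between 0 and 20 points. A patient with no visit after baseline carries the baseline value and is a non-responder under both rules, which keeps q below 1 if there are any such patients.

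**3. Shift in the difference (NBZG minus placebo) relative to non-responder counting** = d1·q1 − d2·q2. The last column assumes that the rates under non-responder counting are truly equal at 44.4% (0.8 × 55.5%) and gives how often the nominal 5% two-sided test with 60 per arm would then reject (normal approximation).

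| Dropout NBZG / placebo | Last-visit response NBZG / placebo | Shift | Rejection |
|---|---|---|---|
| 20% / 20% | 30% / 30% | 0 points | 5.0% |
| 20% / 20% | 50% / 30% | 0.20×0.50 − 0.20×0.30 = +4 points | 7.2% |
| 20% / 20% | 70% / 30% | 0.20×0.70 − 0.20×0.30 = +8 points | 14.1% |
| 30% / 10% | 30% / 30% | 0.30×0.30 − 0.10×0.30 = +6 points | 10.0% |
| 10% / 30% | 30% / 30% | 0.10×0.30 − 0.30×0.30 = −6 points | 10.0% |

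A plus sign favours NBZG. The last row rejects in favour of placebo.

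**4. Power if dropouts are counted as non-responders,** taking the pilot rates as completer rates (an assumption) with equal dropout in both arms and 60 per arm. Power = Φ[(Δ − 1.96·SE0)/SE1], where Δ is the difference, SE0 uses the pooled rate and SE1 the separate rates.

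- No dropout: 84.8% vs 55.5%, power 94.9%.
- 10% dropout: 76.3% vs 50.0%, Δ = 0.264, SE0 = 0.0881, SE1 = 0.0847, power Φ(1.07) ≈ 86%.
- 20% dropout: 67.8% vs 44.4%, Δ = 0.234, SE0 = 0.0906, SE1 = 0.0880, power Φ(0.65) ≈ 74%.

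At 20% dropout, 90% power under non-responder counting would need about 93 per arm.

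**The case against.** The strongest reply is that a gap between LOCF and non-responder counting is not bias against the truth, because the true week-12 status of a lost patient is unknown. That stands. Every shift above is measured against a stated convention. With the pilot rates among completers and last-visit response of 70% vs 30%, the LOCF difference is 0.8 × 29.3 + 8 = 31.4 points and the non-responder difference is 23.4. LOCF then lies 2.1 points above the planned 29.3 and non-responder counting 5.9 below it. The case for changing the rule is that LOCF credits unobserved successes, not that the replacement lies nearer the planned effect.

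A reader might infer that LOCF certainly biases the comparison, perhaps in favour of NBZG. The article does not support this. It gives no dropout or last-visit response by arm, and the shift is zero when both are equal.

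A reader might also infer that every patient taken off medicine for toxicity becomes a carried responder. The article does not say so. Stopping medicine does not end follow-up, and under intention to treat such a patient can attend week 12 and be counted as observed. The problem arises only when the week-12 assessment is missing.

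Finally, non-responder counting is itself single imputation and also treats the imputed status as observed. That stands too, and is why multiple imputation belongs beside it.

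The reply that such detail belongs in a separate analysis plan does not help here: the article itself fixes LOCF, without exception for the primary endpoint.

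**Conclusion.** The point holds as a risk that should be removed, not as a demonstrated bias. LOCF for the binary week-12 ACR50 can overstate both response rates, by up to 20 points per arm at the planned dropout in the extreme case that every dropout carries a response. It can move the treatment difference in either direction. In the illustrated scenarios the shift runs from −6 to +8 points against a planned difference of 29.3. It is zero if dropout and last-visit response are the same in both arms. Those splits are assumptions, and neither direction nor size can be derived from the article. For the continuous scores, carried values are analysed as if measured, so their uncertainty is ignored. The change should be made before unblinding.

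**What to change.** - **Primary ACR50.** Count any randomised patient without a week-12 ACR50 assessment as a non-responder. Patients who stop medicine but are assessed at week 12 keep their observed status.
- **Sensitivity analyses for ACR50.** Multiple imputation, and LOCF in this role only.
- **Continuous scores.** A mixed model for repeated measures on the scheduled visits after baseline: weeks 4, 8 and 12, plus week 16 for scores that can be collected by telephone, since section 2.5.3 makes that visit a call. Terms: arm, visit, arm-by-visit, baseline score and centre.
- **Section 2.4.** Restate the power under the new primary rule, and say whether the pilot rates are completer rates or already count dropouts as failures. If they already do, the scaling in step 4 would count dropout twice.

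The direct cost is analysis wording and some programming, with no change to visits or data collection. The real cost is lower absolute response rates and less power: on the completer-rate assumption, about 86% at 10% dropout and 74% at the planned 20% with 60 per arm, against the 90% stated. Restating the power makes this visible but does not restore it. The sponsor must either accept it, enlarge the trial (about 93 per arm for 90% at 20% dropout), or limit the loss of week-12 assessments.
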